
### Participant timeline {13}

The schedule of enrolment, intervention and visits is summarized in Tables 1 and 2. The duration of the study participation is 44 months (recruitment 38 months + 6 months follow-up).

**Table 1 Tab1:** Participant timeline for the regimen according to Stupp

4.3.1.Stupp regimen	Screening	CHEMO RADIO THERAPY	Visit 1	Visit 2	Visit 3	Visit 4	Visit 5	Visit 6	Visit 7	Visit 8	Visit 9	Visit 10	Visit 11	Visit 12 (EoT)	Follow-up until PD	EoS Visit
Days / Months	**max. 14 D**	**D1-D42** **(M 1–2)**	**D42 + 1 M** (± 1 tweek)	** + 1 M**	** + 1 M**	** + 1 M**	** + 1 M**	** + 1 M**	** + 1 M**	** + 1 M**	** + 1 M**	** + 1 M**	** + 1 M**	** + 1 M**	**Every 3 M** (± 1 tweek)	**PD**
Inclusion/exclusion criteria	X															
Informed consent	X															
Anamnesis^a^	X															
Pregnancy test (serum/urine)	x*	xx*	x	x	x	x	X	x	x	x	x	x	x			
HIV, HBV, HCV test	X**															
Physical and laboratory examination^b^	X**	x***	x	x	x	x	x	x	x	x	x	x	x	x		
ECOG Performance status	X	x	x	x	x	x	x	x	x	x	x	x	x	x		
Extent of surgery^c^	x															
^11^C-MET PET/CT^d^	x															
Quality of life questionnaires^e^	x			x		x		x		x		x		x	x	
MR and RANO evaluation^f^				x (á 3 months)												
Molecular markers^g^	*To be performed during the patient's participation in the study*															
Radiotherapy **(start max. 8 weeks since surgery and max. 2 weeks after planning MR)**		x														
Chemotherapy **(start max. 8 weeks since surgery and max. 2 weeks after planning MR)**		x	x	x	x	x	x	X	x	x	x	x	x	x		
Adverse events		x	x	x	x	x	x	X	x	x	x	x	x	x	x	x
PoF analysis^h^																x

The description of performed examinations:

^*^The pregnancy test will be performed at the center (1. As part of the screening phase before 11C-methionine applications and 2. Before the 1st application of concomitant chemoradiotherapy)

^**^Laboratory analysis incl. tests for HIV, HBV and HCV will be performed in the screening phase if they have not been performed in the previous 5 days

^***^Laboratory analysis (blood count + differential + biochemistry) will be performed every week as part of CHRT. Physical examination will be performed on D1 and D21 (if not performed in the previous 5 days)

^a^Anamnesis

Collection of anamnestic data will take place following standard clinical practice. Taking a family history will focus on the familial occurrence of malignancies and genetic syndromes. As part of the personal anamnesis, pre-existing severe diseases will be recorded even at the time of diagnosis; a pharmacological anamnesis and information on allergies will automatically be included. Data will also be collected regarding substance abuse and social and work anamnesis

^b^Physical and laboratory examination

Physical examination + neurological examination + height/weight/vital functions: BSA calculation, blood pressure, pulse, respiratory rate, body temperature;

Performance status: according to ECOG 0–2; Laboratory examination: blood count including differential count, Na, K, Cl, urea, creatinine, glucose, total bilirubin, ALT, AST, ALP, amylase, LD, albumin, total protein, CRP

^c^Scope of operation

Evaluation according to postoperative MR (performed within 72 h after surgery):

Gross Total Resection: complete macroscopic resection

Subtotal Resection: resection of ≥ 90% of the tumor

Partial Resection: resection of < 90% of tumor (biopsy only = exclusion criterion)

^d11^C-MET PET/CT

^11^carbon radiolabelled methionine positron emission tomography/computer tomography

^e^Quality of life questionnaire

These are standardized questionnaires assessing the quality of life of oncology patients, according to the EORTC. Official versions of the questionnaires in Czech are available. These questionnaires can be completed at home. The basic questionnaire (EORTC QLQ-C30 Czech) contains 30 questions with the possibility of answering a degree of four points or a seven-point Likert scale. Part of the quality of life questionnaires is also a module of an additional 20 questions optimized to assess the quality of life of neuro-oncology patients

^f^Magnetic Resonance Imaging and assessment of RANO criteria

^g^Molecular markers

Immunohistochemical labeling of GFAP, Ki-67, IDH1 and ATRX, PDL1 protein expression by immunohistochemistry, mutational status of TERT and IDH2 genes and then IDH1 in immunohistochemically positive patients by Sanger sequencing, methylation status of the MGMT promoter and 1p/19q codeletion

^h^PoF analysis

Spatial evaluation of recurrence in relation to the area irradiated with a high dose of radiation (patterns of failure, PoF) is performed by a radiotherapist. MR defining progression according to RANO (MRRANO) criteria is used to analyze PoF, specifically T1-weighted sequence with contrast medium administration

Standard image fusion is performed in the radiotherapy planning system: MRRANO is registered to the original planning CT. The fusion is focused on the calf area (preferential choice of Hounsfield HU units in the bone band)

**Table 2 Tab2:** Participant timeline for the regimen according to Perry

4.3.2. Perry regimen	Screening	CHEMO RADIO THERAPY	Visit 1	Visit 2	Visit 3	Visit 4	Visit 5	Visit 6	Visit 7	Visit 8	Visit 9	Visit 10	Visit 11	Visit 12 (EoT)	Follow-up until PD	EoS Visit
Days / Months	**max. 14 D**	**D1-D21** **(M 1–2)**	**D21 + 1 M** (± 1 week)	** + 1 M**	** + 1 M**	** + 1 M**	** + 1 M**	** + 1 M**	** + 1 M**	** + 1 M**	** + 1 M**	** + 1 M**	** + 1 M**	** + 1 M**	**Every 3 M** (± 1 week)	**PD**
Inclusion/exclusion criteria	x															
Informed consent	x															
Anamnesis^a^	x															
Pregnancy test (serum/urine)	x*	x*	x	x	x	x	x	x	x	x	x	x	x			
HIV, HBV, HCV test	X**															
Physical and laboratory examination^b^	X**	x***	x	x	x	x	x	x	x	x	x	x	x	x		
ECOG Performance status	x	x	x	x	x	x	x	x	x	x	x	x	x	x		
Extent of surgery^c^	x															
^11^C-MET PET/CT^d^	x															
Quality of life questionnaires^e^	x			x		x		x		x		x		x	x	
MR and RANO evaluation^f^				x (á 3 months)												
Molecular markers^g^	*To be performed during the patient's participation in the study*															
Radiotherapy **(start max. 8 weeks since surgery and max. 2 weeks after planning MR)**		x														
Chemotherapy **(start max. 8 weeks since surgery and max. 2 weeks after planning MR)**		x	x	x	x	x	x	x	x	x	x	x	x	x		
Adverse events		x	x	x	x	x	x	x	x	x	x	x	x	x	x	x
PoF analysis^h^																x

The description of performed examinations:

^*^The pregnancy test will be performed at the center (1. As part of the screening phase before 11C-methionine applications and 2. Before the 1st application of concomitant chemoradiotherapy)

^**^Laboratory analysis incl. tests for HIV, HBV and HCV will be performed in the screening phase if they have not been performed in the previous 5 days

^***^Laboratory analysis (blood count + differential + biochemistry) will be performed every week as part of CHRT. Physical examination will be performed on D1 and D21 (if not performed in the previous 5 days)

^a^Anamnesis

Collection of anamnestic data will take place following standard clinical practice. Taking a family history will focus on the familial occurrence of malignancies and genetic syndromes. As part of the personal anamnesis, pre-existing severe diseases will be recorded even at the time of diagnosis; a pharmacological anamnesis and information on allergies will automatically be included. Data will also be collected regarding substance abuse and social and work anamnesis

^b^Physical and laboratory examination

Physical examination + neurological examination + height/weight/vital functions: BSA calculation, blood pressure, pulse, respiratory rate, body temperature;

Performance status: according to ECOG 0–2; Laboratory examination: blood count including differential count, Na, K, Cl, urea, creatinine, glucose, total bilirubin, ALT, AST, ALP, amylase, LD, albumin, total protein, CRP

^c^Scope of operation

Evaluation according to postoperative MR (performed within 72 h after surgery):

Gross Total Resection: complete macroscopic resection

Subtotal Resection: resection of ≥ 90% of the tumor

Partial Resection: resection of < 90% of tumor (biopsy only = exclusion criterion)

^d11^C-MET PET/CT

^11^carbon radiolabelled methionine positron emission tomography/computer tomography

^e^Quality of life questionnaire

These are standardized questionnaires assessing the quality of life of oncology patients, according to the EORTC. Official versions of the questionnaires in Czech are available. These questionnaires can be completed at home. The basic questionnaire (EORTC QLQ-C30 Czech) contains 30 questions with the possibility of answering a degree of four points or a seven-point Likert scale. Part of the quality of life questionnaires is also a module of an additional 20 questions optimized to assess the quality of life of neuro-oncology patients

^f^Magnetic Resonance Imaging and assessment of RANO criteria

^g^Molecular markers

Immunohistochemical labeling of GFAP, Ki-67, IDH1 and ATRX, PDL1 protein expression by immunohistochemistry, mutational status of TERT and IDH2 genes and then IDH1 in immunohistochemically positive patients by Sanger sequencing, methylation status of the MGMT promoter and 1p/19q codeletion

^h^PoF analysis

Spatial evaluation of recurrence in relation to the area irradiated with a high dose of radiation (patterns of failure, PoF) is performed by a radiotherapist. MR defining progression according to RANO (MRRANO) criteria is used to analyze PoF, specifically T1-weighted sequence with contrast medium administration

Standard image fusion is performed in the radiotherapy planning system: MRRANO is registered to the original planning CT. The fusion is focused on the calf area (preferential choice of Hounsfield HU units in the bone band)

The modification consists of changing the irradiation plan.

Two chemoradiotherapy regimens of concomitant chemoradiotherapy with temozolomide are permissible at the discretion of the attending physician.

Stupp's regimen can be extended to 12 cycles of adjuvant temozolomide due to the unification of the possible length of administration of adjuvant temozolomide itself and thus minimizing the occurrence of bias in the length of adjuvant treatment between younger and older/frail groups in the clinical study.

Since 2005, when temozolomide was registered based on the study with 6 cycles of adjuvant temozolomide, a number of phase 3 studies were conducted, where it was possible to extend this adjuvant period up to 12 cycles. On the other hand, in patients without REP, extension of adjuvant chemotherapy up to 12 cycles is currently not recommended [2].

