**Methods:**

This study is a nonrandomized, open-label, parallel-setting, prospective, monocentric clinical trial. The main aim of this study was to refine the diagnosis in patients with GBM with REP and to optimize subsequent radiotherapy planning.

Glioblastoma patients who develop REP within approximately 6 weeks after surgery will undergo ^11^C-methionine positron emission tomography (PET/CT) examinations. Target volumes for radiotherapy are defined using both standard planning T1-weighted contrast-enhanced MRI and PET/CT. The primary outcome is progression-free survival defined using RANO criteria and compared to a historical cohort with REP treated without PET/CT optimization of radiotherapy.

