### Sample size {14}

A historical retrospective cohort included 44 patients with REP who were indicated for adjuvant chemoradiotherapy (Arm Ahist). The median PFS in this cohort was 4.9 months. Assuming that the time distribution in the Experimental Arm follows a proportional hazard model, a significance level of 5%, and a power of 80%, 65 events are needed to detect a hazard ratio of 1.65 (i.e., median PFS in the Experimental Arm of 8 months). With an assumed recruitment of 38 months and a follow-up duration of six months, 67 patients are needed based on the historical cohort. With the expected screening failure rate of 5% and a dropout rate of 5%, approximately 75 patients with confirmed REP should be enrolled.

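### Trial-arm progression is read on a 3-monthly MR schedule that could not have governed the 2014–2018 comparator, and the plan compares recorded dates, so any difference in scan timing biases PFS in either direction

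*Protocol article*

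**What the plan says.** The Abstract sets the endpoint and comparator: "The primary outcome is progression-free survival defined using RANO criteria and compared to a historical cohort with REP treated without PET/CT optimization of radiotherapy". Outcomes {12} and Statistical methods {20a} time PFS from the start of radiotherapy to progression or death. Trial design {8} calls the comparison confirmatory.

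Participant timeline {13}, Tables 1 and 2, has a row "MR and RANO evaluation^f" with one entry in the Visit 2 column, marked as repeating every 3 months. Visit 1 is one month after day 42 (six-week regimen) or day 21 (three-week regimen), and Visit 2 is one month later.

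On the comparator, Sample size {14} says: "A historical retrospective cohort included 44 patients with REP" and "The median PFS in this cohort was 4.9 months". Study setting {9} dates that cohort to 2014–2018 and the start of recruitment to October 2020. The article does not say when or how often the historical patients were scanned. The target is: "65 events are needed to detect a hazard ratio of 1.65 (i.e., median PFS in the Experimental Arm of 8 months".

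Statistical methods {20a} names Kaplan-Meier, log-rank or Gehan-Wilcoxon, and Cox. The only sensitivity analysis mentioned, in {20c}, is imputation for missing data.

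**The concern.** MR-detected progression is dated when a scan shows it, not when it happens. The article sets the scan schedule in one arm and takes the other arm's dates as they come. The gain sought is about one scan interval, and only one scheduled scan falls before the historical median of 4.9 months, so the measurement is about as coarse as the effect.

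If the historical patients were scanned earlier or more densely, identical disease would look like a benefit of PET-guided planning. If they were scanned later, a real benefit could be hidden. Adjusting for patient characteristics removes neither. The two regimens within the trial arm also sit on grids three weeks apart.

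**Working it through.** **1. The plan's own figures.** The gain sought is 8 − 4.9 = 3.1 months, and 8/4.9 = 1.63, close to the stated 1.65. Freedman's formula at two-sided 5% and 80% power gives (1.96 + 0.84)² × (2.65/0.65)² ≈ 131 events in total, or 65.5 per arm at 1:1. So 65 is reproduced as a per-arm figure. A one-sided 5% comparison with about 40 fixed historical events gives 64, so that also fits. Nothing below depends on which was meant.

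**2. When the trial arm is read** (30.44 days per month, table taken literally).
- Six-week regimen: 42/30.44 + 2 = 3.38 months, then 6.38 and 9.38.
- Three-week regimen: 21/30.44 + 2 = 2.69 months, then 5.69 and 8.69.

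**3. Median, no true effect.** Assume exponential times with true median 4.9 in both arms and 70% on the six-week regimen. S(t) = exp(−ln 2 × t/4.9) gives S(3.38) = 0.620, S(5.69) = 0.447 and S(6.38) = 0.406.
- Recorded trial-arm curve at 5.69: 0.7 × 0.620 + 0.3 × 0.447 = 0.568.
- At 6.38: 0.7 × 0.406 + 0.3 × 0.447 = 0.418. The recorded median is therefore 6.38.
- Against continuous historical dating the spurious gain is 6.38 − 4.9 = 1.48 months (48% of 3.1). If all patients were on the three-week grid it is 5.69 − 4.9 = 0.79 (25%).
- The stated 4.9 is itself a recorded median, so a like-for-like comparison puts the historical arm on a schedule too. With a first MR 1 month after radiotherapy ends (2.38 or 1.69 months), it reads 5.38 if scans are then 3-monthly, 6.38 if 2-monthly and 5.38 if monthly. The spurious gains are 1.0, 0 and 1.0 month.

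**4. Test error, no true effect.** Simulation with 67 v 44 patients, the assumptions of step 3, trial arm censored uniformly between 6 and 44 months, and 1,500–2,000 trials per scenario. Percentage of trials significant in favour of PET (two-sided 5%, so nominally 2.5%):

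| Assumed historical MR | Log-rank | Log-rank, 30% of progressions dated exactly | Gehan-Wilcoxon |
|---|---|---|---|
| Same grid as trial | 2.6–2.9 | 2.9–3.3 | 2.1 |
| First at 1 month after RT, then 3-monthly | 10.3–10.5 | 6.5 | 16 |
| First at 1 month after RT, then 2-monthly | 9.6–10.1 | 7.0–8.1 | 15 |
| First at 1 month after RT, then monthly | 19–20 | 12.3–12.5 | 32 |
| Continuous | 39 | 19–20 | 54 |

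Ranges are from two separate runs; a further repeat put the three 1-month rows with exact dating at about 5–12%. The corresponding spurious hazard ratios (historical v trial) are about 1.09–1.10 for 2- to 3-monthly scans and 1.18 for monthly scans. On the log scale these are ln 1.09/ln 1.65 = 17%, ln 1.10/ln 1.65 = 19% and ln 1.18/ln 1.65 = 33% of the target effect.

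**5. The other direction.** If the historical grid runs one month later than the six-week trial grid, with 20% of events dated exactly and true medians of 3.5–4.9, the log-rank favours PET in 0.3–1.0% of trials and goes against it in 6–12%.

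**6. Sensitivity to calibration.** If the historical recorded median is instead forced to 4.9 (six-week grid, no censoring), the log-rank favours PET in 33% of trials with 2-monthly historical scans (16% with 20% of events exact) and in 23% with unaligned 3-monthly scans (13%). With unaligned 4-monthly scans and 20% exact, the trial-arm median shifts by −1.5 months, while the log-rank favours PET in 7.1% of trials and goes against it in 1.7%. Median and test need not move the same way.

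**The case against.** The strongest reply is that the article never says that the historical schedule differed. That stands: the schedule is not given, and an identical one removes the bias. A 4.9-month median lies off the trial's grid points, but deaths and mixed regimens can explain that.

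A reader might infer that the schedule alone could produce much of the 3.1-month gain. The documents do not support this. The figure of about half sets a grid-read 6.4 against a true 4.9, whereas the protocol's 4.9 is a recorded median that already contains scan delay.

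A reader might also infer that trial-arm progression can be dated only at the grid points. That is too strong. Deaths count at their own date, clinical examination is about monthly, the end-of-study visit is set at progression, and nothing bars unscheduled MR. The start of the grid also rests on one table cell that may be a merged cell in the original; the 3-month spacing does not depend on it.

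Rules for dating progression may sit in the full protocol or SAP, and their absence from an article is no fault. The point rests instead on what the article fixes: a schedule in one arm, a comparator collected before it, and tests applied to recorded dates. OS against the historical arm is already planned and does not depend on scan dates, but it is secondary.

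**Conclusion.** The concern holds as an open risk of bias in the primary comparison. It is not a demonstrated bias, and its direction is unknown. Matching schedules give none. Later historical scans, or sparser ones from the same first date, work against PET; earlier or denser ones work in its favour.

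Under the assumed schedules in step 4, the log-rank favours PET under no effect in about 10–20% of trials instead of about 2.5–3%, or about 5–12% if 30% of events are dated exactly. Gehan-Wilcoxon, which the plan also allows, is affected more. The median shift is about 0–1 month, and about 1.5 months at most if historical progression was dated almost continuously.

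These sizes rest on exponential times, a 70/30 regimen mix, a literal reading of the tables and invented historical schedules. They are ranges, not estimates. The error rate is the stronger argument; the effect on the median is modest.

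**What to change.** For both arms, extract from the records, where available, the date of the last MR without progression and of the first MR with progression. Report the achieved MR intervals per arm.

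Prespecify one supporting PFS analysis that is robust to scan timing:
- an interval-censored proportional-hazards model on the interval from last negative to first positive MR, with deaths at their exact date; or
- progression in both arms assigned to one common grid counted from the start of radiotherapy.

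Report it beside the primary test and read both together with OS. It need not replace the primary analysis or become a condition for claiming benefit; that is the sponsor's choice.

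The cost is a few date fields for about 110 patients (44 + 67 = 111), one extra model and a slightly wider interval for the hazard ratio. No new scans are needed.

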### Sample size {14}

A historical retrospective cohort included 44 patients with REP who were indicated for adjuvant chemoradiotherapy (Arm Ahist). The median PFS in this cohort was 4.9 months. Assuming that the time distribution in the Experimental Arm follows a proportional hazard model, a significance level of 5%, and a power of 80%, 65 events are needed to detect a hazard ratio of 1.65 (i.e., median PFS in the Experimental Arm of 8 months). With an assumed recruitment of 38 months and a follow-up duration of six months, 67 patients are needed based on the historical cohort. With the expected screening failure rate of 5% and a dropout rate of 5%, approximately 75 patients with confirmed REP should be enrolled.

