### Explanation for choice of comparator {6b}

This study is an open-label prospective clinical trial. The experimental drug ^11^C-methionine PET/CT will be administered to all patients recruited to this study and compared to the cohort consisting of a historical group of GBM patients with REP collected in the period 2014–2018.

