### Eligibility criteria {10}

A patient may be included in the clinical trial if they meet all of the following criteria:The participant is a person with a histologically proven diagnosis of glioblastoma (GBM) according to WHO 2016.The participants are male or female and aged 18 years or older.Performance status (PS) according to ECOG (Eastern Cooperative Oncology Group) 0–2.Healed operation wound.Postoperative MR up to 72 h.Indication for adjuvant chemoradiotherapy.The participants must express his/her informed consent and sign the form before the screening period.Rapid early progression was detected.The participants must achieve the following values of laboratory parameters in the peripheral blood during the screening period:neutrophils (total count) ≥ 1500/mm.3platelets (total count) ≥ 100,000/mm.3hemoglobin ≥ 9.0 g/dLserum creatinine ≤ 1.5 × of upper limit of normal (ULN)total bilirubin ≤ 1.5 × ULN, unless documented Gilbert's syndrome, for which bilirubin ≤ 3 × ULN is permitted AST/ALT ≤ 3 × ULN

The exclusion criteria were as follows:Prior brain surgery.Prior brain radiotherapy.The history of active/currently treated cancer (solid tumor) was as follows: nonmelanoma skin cancer, in situ bladder carcinoma, in situ gastric cancer, in situ colorectal carcinoma, in situ cervical carcinoma, and in situ breast cancer.Any systemic disease or health condition that might pose a risk for anticancer therapy and imaging techniques (MRI, MET PET).Patients must not have substance abuse disorders that would interfere with cooperation with the requirements of the trial.Patients must not have any evidence of ongoing (active) infection (HIV, hepatitis A, B, C).Pregnant and/or breastfeeding women.Patients who disagreed and refused to sign an informed consent form.

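### Arm Ahist and its 4.9-month median are not stated to meet the trial's own entry criteria, so the confirmatory PFS comparison may include controls the trial would refuse, and any such mismatch would be expected to favour PET

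*Protocol article*

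**What the plan says.** Explanation for choice of comparator {6b} says the trial arm will be "compared to the cohort consisting of a historical group of GBM patients with REP collected in the period 2014–2018". Sample size {14} adds one further condition: "A historical retrospective cohort included 44 patients with REP who were indicated for adjuvant chemoradiotherapy (Arm Ahist"). It continues: "The median PFS in this cohort was 4.9 months". These are the only descriptors of Arm Ahist: REP, the years 2014–2018, and an indication for chemoradiotherapy.

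The Experimental Arm must satisfy more. Eligibility criteria {10} repeats the chemoradiotherapy indication and REP. It adds ECOG 0–2, a healed wound, postoperative MR within 72 hours, and blood limits: "The participants must achieve the following values of laboratory parameters in the peripheral blood during the screening period". It excludes active infection, certain cancers, prior brain radiotherapy, and systemic conditions that put therapy or imaging at risk. Footnote c of Tables 1 and 2 (Participant timeline {13}) also makes biopsy-only surgery an exclusion. The treatment rows of those tables give timing limits: "start max. 8 weeks since surgery and max. 2 weeks after planning MR".

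Trial design {8} calls the comparison with the historical cohort confirmatory. Section {20b} says adjusted analyses are not planned, whereas {20a} names a multivariable Cox model.

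**The concern.** Without randomisation, the comparison isolates PET-based planning only if the two groups would otherwise have had similar PFS. ECOG and laboratory limits, and exclusions for infection or comorbidity, mainly remove patients with a poorer outlook. If they are applied to the trial arm alone, that arm would be expected to do better even if PET planning does nothing.

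Two quantities are exposed. One is the false-positive rate of the primary test. The other is the control median used for sizing: if some of the 44 would not have been eligible, 4.9 months understates what eligible patients achieve without PET.

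The descriptive comparison of patient characteristics in {20a} would reveal an imbalance but not remove it. Covariate adjustment, if it is done at all, does not fully solve the problem, because a control who would have failed screening has no counterpart in the trial arm.

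**Working it through.** **1. The plan's own figures.** Inputs from {14}: hazard ratio 1.65, 5% significance (sidedness not stated; two-sided taken here), 80% power, medians 4.9 and 8 months, 38 + 6 months.

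- Events per arm (Freedman): (1.96 + 0.84)² × (2.65/0.65)² / 2 = 65.2, matching 65.
- Patients: 65 / (1 − exp(−ln 2 × 44/8)) = 66.5, rounded up to 67.
- Enrolment: 67/0.90 = 74.4, rounded up to 75.

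So the 4.9-month median feeds directly into the stated size.

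**2. Entry rules side by side.**

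| Rule | Experimental Arm | Arm Ahist, as described |
|---|---|---|
| REP | required | required |
| Indication for chemoradiotherapy | required | required |
| ECOG 0–2 | required | not stated |
| Laboratory limits | required | not stated |
| No active infection, excluded cancer or risky comorbidity | required | not stated |
| Not biopsy only | required | not stated |
| MR within 72 h of surgery | required | not stated, but largely implied by how the Introduction defines REP |

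**3. Size under stated assumptions.** The documents give no ineligible share, so it is varied. Let a share f of Ahist be ineligible with k times the hazard of eligible controls, PFS exponential, and the whole-cohort median held at 4.9 months. The eligible-control median m solves

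(1 − f) · 2^(−4.9/m) + f · 2^(−4.9k/m) = 0.5.

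Example, f = 0.2 and k = 2: with x = 2^(−4.9/m), 0.8x + 0.2x² = 0.5 gives x = (−0.8 + √1.04)/0.4 = 0.5495. Then m = 4.9 × ln 2 / 0.5987 = 5.67 months.

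Each setting was simulated with 4,000 trials: 44 controls all with events; 67 trial patients accrued uniformly over 38 months with cut-off at month 44; log-rank z beyond 1.96 in favour of the trial arm. For the false-positive rate, the trial median equals m (no PET effect) and all 44 controls are used. For power, controls are restricted to the eligible and the effect is held at the planned ratio 8/4.9 = 1.63. Ranges are over k = 1.5 to 3.

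| Ineligible share | Eligible control median (months) | False finding for PET, all 44 | Power, restricted controls |
|---|---|---|---|
| none | 4.9 | about 3% | 68–69% |
| 5% | 5.0–5.2 | 4–5% | 66–68% |
| 10% | 5.1–5.5 | 4–6% | 65–67% |
| 20% | 5.3–6.2 | 6–12% | 60–62% |
| 30% | 5.6–7.0 | 8–22% | 57–59% |

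Separate runs differ by about a percentage point. After restriction the false-positive rate is again about 3% (2.6–3.5%).

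**4. Check on the power column.** Under uniform accrual, 82.6% of trial patients with an 8-month median have an event: 67 × 0.826 = 55.3. Power is Φ(√[1/(1/55.3 + 1/d)] × ln 1.633 − 1.96), with d control events.

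- d = 44: 4.95 × 0.490 − 1.96 = 0.47, or 68%.
- d = 44 × 0.8 = 35.2: 4.64 × 0.490 − 1.96 = 0.31, or 62%.
- d = 44 × 0.7 = 30.8: 4.45 × 0.490 − 1.96 = 0.22, or 59%.

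The baseline is below 80% because the control arm has 44 patients, not 65 events, and because uniform accrual yields about 55 trial events. That is a separate matter from this point.

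**The case against.** The strongest reply is that silence is not evidence. The article condenses a fuller protocol, and the centre's retrospective analysis is cited but not shown; either may define the cohort more tightly. This stands as a limit: a reader might infer that Ahist is known to be broader than the trial population, or that the comparison is already tilted, and the documents do not show that any of the 44 would fail. It does not dispose of the point, because {6b} and {14} do state a selection rule for the comparator of a confirmatory test, and that rule is wider than the trial's.

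The filters also overlap. The shared chemoradiotherapy indication already keeps the least fit out of both groups, and the trial admits frail and elderly patients through the Perry regimen. This stands and argues for the lower part of the range.

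The nearest figure in the plan is the 5% screening failure rate in {14}. At 5%, the false-positive rate is only about 4–5%. That figure is a planning assumption for prospective patients, however, and does not bound a retrospective series.

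A reader might also count the 8-week and 2-week limits as one-sided filters favouring PET. They are timings in the visit tables, not criteria in {10}. The Introduction describes usual care as starting 4–6 weeks after surgery, with planning MR a few days before radiotherapy, so they may exclude few controls. PFS is counted from the start of radiotherapy in both groups, so the direction of any effect is uncertain.

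Finally, one could hold the trial median at 8 months while raising the control median, and report power falling to 36% (20% ineligible, twice the hazard) or 9% (30%, three times). Most of that fall comes from shrinking the assumed PET effect. The plan sizes on a hazard ratio, and at a constant ratio the loss is modest and reflects the smaller control arm.

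**Conclusion.** The concern holds in a limited form. As described, Arm Ahist is selected by fewer rules than the trial arm, nothing in the document applies the remaining rules to it, and {20b} plans no adjustment. Any resulting mismatch would be expected to favour PET, most clearly through ECOG and the laboratory limits. Whether a mismatch exists, and how large it is, cannot be determined from the document.

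The plausible effect runs from slight, if about 5% of the 44 would be refused, to a false-positive rate several times nominal, if 30% would be refused at three times the hazard. These figures rest on exponential PFS, a pooled median fixed at 4.9 months and assumed shares and hazards; they show sensitivity and do not estimate the bias. The point should be settled because the check is cheap and the comparison is confirmatory.

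**What to change.** State in {6b} and {14} that the primary comparator is the subset of Ahist meeting every trial entry criterion that can be read from the records: ECOG 0–2, pre-treatment laboratory values, postoperative MR within 72 hours, not biopsy only, no prior brain radiotherapy, and no active infection or excluded cancer. Use a fixed checklist applied by someone without access to the PFS data; this matters because the cohort's overall PFS is already known. Report the subset's size, median PFS and resulting power. Keep all 44 as a sensitivity analysis. Treat the surgery-to-radiotherapy and planning-MR-to-radiotherapy intervals as a further sensitivity restriction. Reconcile {20a} with {20b} on whether a multivariable model is planned.

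The cost is a review of 44 charts and a wording change; no new patients or procedures are needed. The downside is a smaller control arm, with the loss of power at the planned hazard ratio shown in the last column of the table above. Recruitment was due to end in February 2024, so the restated power may serve interpretation more than enrolment. If all 44 qualify, one sentence saying so closes the matter.
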